**Method/design:**

This study aims to establish or rule-out cmDNA as a representative of the gut microbiome. In a prospective, single-arm crossover trial, effects of dairy product withdrawal and reintroduction of a yoghurt with a known consortium of bacteria will be assessed in healthy volunteers aged 18–65. Participants will first abstain from all dairy products, a phase expected to reduce yogurt-associated cmDNA in the bloodstream. Yogurt will then be reintroduced, during which reappearance of cmDNA of specific bacteria (especially LGG, LA-5 and BB-12) is anticipated. Shotgun metagenomic sequencing will be used to track cmDNA dynamics over time. This longitudinal sampling approach will provide experimental evidence supporting the existence and responsiveness of the circulating microbiome, while also revalidating the bioinformatic pipeline used for its analysis.

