### Study design

2.1

We will perform a within-subjects crossover trial with a single arm to study the effect of yogurt on the blood and fecal YDB levels in healthy volunteers. Participants will first undergo a 10-day period of dairy product withdrawal. Given that the half-life of bacterial DNA in blood is likely less than 24 h, a 10-day withdrawal period should be sufficient to substantially reduce circulating DNA fragments originating from *L. lactis*. Following the reintroduction of dairy (via yogurt consumption that is host to LGG, LA-5 and BB-12 cultures), we expect these specific bacteria and other YDB DNA to reappear in the bloodstream. While the precise kinetics of this reappearance are not yet known, our study is designed to detect these temporal changes and establish a foundation for understanding the dynamic relationship between dietary intake, the gut microbiome, and the blood microbiome.

This study is approved by the ethics committee of Erasmus Medical University Center Rotterdam in May 2025 (NL88008.078.24) and is registered at www.clinicaltrials.gov (NCT06944002), hence prior to participant's enrollment. This study will be conducted in accordance with the principles of the Declaration of Helsinki (75th WMA General Assembly, Helsinki, Finland, October 2024) and the Medical Research Involving Human Subjects Act (WMO). Interested volunteers will be provided with detailed information about the study and will give written informed consent prior to participation.

Participants will be studied at multiple time points using a within-subject crossover design (Fig. 1). At baseline, prior to any dietary intervention, blood and stool samples will be collected. Following this, participants will abstain from all dairy products for 10 days, after which a second set of blood and stool samples will be collected to confirm the expected disappearance of YDB DNA from both fecal and circulating microbial DNA pools.

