#### Primary objective

2.5.1

The primary objective is to examine yogurt-dependent bacterial (YDB) DNA counts in fecal and blood samples before and after dairy consumption. YDB, such as *Lactococcus lactis*, are transient residents of the human gut, only present following dairy intake, and therefore represent modifiable components of the intestinal microbiome. Detection of YDB DNA fragments in the bloodstream after dairy reintroduction will provide definitive evidence on the extent to which the blood microbiome reflects relevant changes in the intestinal microbiome. In this specific study, the use of a commercial yoghurt (but verified by independent agar growth testing) containing a defined consortium of bacteria adds signature species whose detection provides convincing signals in this respect.

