#### Long-term objective

2.5.3

The ultimate objective is to develop technology capable of reliably characterizing the dynamics of microbiomes residing in and on the human body. This study will evaluate the extent to which this goal is achievable. It is anticipated that non-dairy-dependent microorganisms will exhibit relatively stable levels over time, whereas dairy-dependent organisms such as *Lactococcus* and *Bifidobacterium* species are expected to show measurable changes. Detecting will be critical for assessing the utility of blood microbiome technology in generating comprehensive, integrative descriptions of human-associated microbiomes.

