### Power analysis

2.6

This is a pilot study. This research has never been conducted before, making it difficult to determine a definite sample size. Based on published studies showing significant change in the relative abundance of gut microbiome at the phylum level upon consumption of fermented milk in 6 volunteers (Firmicutes and Bacteroidetes; p < 0.05 when comparing milk consumption vs. baseline) [20], and that the relative abundance of Bifidobacterium species increased following the consumption of human milk oligosaccharides by 7 volunteers over 7 days (p < 0.05 when comparing four type of milk concentrations with baseline) [21], we have chosen to include 10 volunteers for this study. If this is not sufficient to convincingly demonstrate trends of *Lactococcus lactis* DNA during 7 days of milk consumption intervention, then blood microbiome studies may not be powerful enough to show meaningful changes in intestinal microbiome composition.

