**Fig. 3 fig3:**
[figure not shown]
Pipeline designed to validate (circulating microbial DNA) cmDNA as a biomarker of the gut microbiota. A. In-vitro yogurt DNA spike-in control. To assess whether intestinal bacterial DNA enters the circulation and is detectable in the blood, DNA extracted from three commercial yogurt samples of the same batch will be pooled based on concentration, serially diluted, and spiked into participant blood samples (e.g., from the pre-intervention visit) prior to DNA extraction. These spiked samples, together with non-spiked baseline blood DNA sample and pooled yogurt DNA, will undergo shotgun sequencing and taxonomic profiling. This provides both quantitative and qualitative benchmarks for detection sensitivity and specificity. B. Reference controls without the spike in. To explore the existence of a core blood microbiome and distinguish the true microbial signals from background noise, the study includes serval refence controls, which will be processed without added microbial DNA or any artificial spike-in, maintaining its original state to serve as benchmark background signal and classification fidelity: (i) placenta blood as negative control; (ii) blood from patients infected with known viruses as a positive control (blood will be obtained from the Erasmus MC virology department); (iii) human-deprived organoids to assess database classification accuracy and text whether human genomic sequences are misclassified as bacterial in tools like Kraken 2; (iv) whole blood from healthy pigs as a translational non-human host control, based on the hypothesis that pigs may harbor a core cmDNA signature due to dietary and physiological similarities with human. This also reflects the growing relevance of pigs as organ donors in translational research; and (v) rat blood as a preclinical non-human host control, representing a widely used model in experimental and pharmacological studies.

To further evaluate the sensitivity and specificity of the entire blood microbiome analysis pipeline, from DNA extraction to data interpretation, a defined microbiome standard (e.g., ZymoBIOMICS Microbial Community DNA Standard) will be included. This benchmark will enable assessment of extraction efficiency, sequencing accuracy and taxonomic profiling cross the pipeline.

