Because the blood microbiome may be less than 5 % of the entire blood DNA, interpretation of such low microbial biomass is challenged by potential environment contamination (e.g., lab equipment and kitome) [22,23]. In addition, the definition of a core blood microbiome is further complicated by that the assembled genomes of many bacteria (especially older assemblies) are contaminated by human DNA sequences, leading to false-positive results. The latter issue is considered the biggest problem in the analysis and interpretation of blood microbiomes [14]. The current study, because of its longitudinal character and its reliance on the introduction of defined species with relatively novel assemblies in the database, is designed to provide of proof-of-principle on whether these problems can be overcome. Further, additional power will be added to the current study by introduction of additional controls: we will include a series of reference controls designed to account for all potential sources of contamination and misinterpretation described above (Fig. 3).2DNA extraction and shotgun sequencing

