#### Microbiome characterization

2.8.2

1Blood Lactococcus and other microbial DNA raw data processing

Raw Illumina sequencing reads will be processed using Readfq to remove poor quality bases (threshold ≤38 bp), reads with excessive N bases, and significant adaptor overlaps. Host-derived reads will be filtered using Bowtie2.2.4 software with parameters: -end-to-end, --sensitive, -I 200, -X 400 [26,27].2Metagenome assembly

Clean reads will be assembled into Scaffolds using MEGAHIT with -presets meta-large option. Scaffolds will be converted into scaftigs by removing N-containing regions [28,29]. Reads will be mapped back to scaffolds using Bowtie, and fragments <500 bp will be excluded from further analysis [30,31].3Gene prediction and abundance calculation

Scaftigs ≥500 bp will be analyzed for open reading frames (ORFs) using MetaGeneMark, filtering out those <100 nt [32,33]. CD-HIT will be used to cluster and remove redundant genes, generating a non-redundant gene catalogue [34,35]. Clean reads will be mapped to this catalogue using Bowtie2, and genes with ≤2 mapped reads will be excluded. Gene abundances will be calculated as described previously [31].4Taxonomy prediction

Unigenes will be taxonomically annotated using the Kraken2 database [36], with further validation against the NCBI NR database [37]. The LCA algorithm in MEGAN [38] will be used for accurate species-level assignment. Taxonomic profiles will include relative abundances and gene counts for all taxa, with specific attention to YDB.

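### The expected signal is three named yogurt cultures (LGG, LA-5, BB-12), but the stated pipeline assigns only to species, so a rise in yogurt-dependent DNA cannot be attributed to the supplied cultures

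*Protocol article*

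**What the plan says.** **Target.** The Abstract (Method/design) states that "reappearance of cmDNA of specific bacteria (especially LGG, LA-5 and BB-12) is anticipated". Section 2.1 describes reintroduction "via yogurt consumption that is host to LGG, LA-5 and BB-12 cultures". The Discussion refers to the probiotic strains in the yogurt as a kind of spike-in, and plans to correlate the blood signal with the amount of these bacteria in the intestine. Two other places argue at species level. Section 2.5.1 says that the commercial yogurt "adds signature species whose detection provides convincing signals in this respect", and section 2.8.1 points to "its reliance on the introduction of defined species with relatively novel assemblies in the database".

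**Read-out.** Section 2.8.2 clusters genes into a non-redundant catalogue, maps reads to it and annotates with Kraken2 and NCBI NR. Then: "The LCA algorithm in MEGAN [38] will be used for accurate species-level assignment". Section 2.8.4 applies the same pipeline to stool.

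**What counts as YDB.** Section 2.5.1 gives *Lactococcus lactis* as an example and describes YDB as present only after dairy intake. Section 2.5.3 expects that "dairy-dependent organisms such as *Lactococcus* and *Bifidobacterium* species are expected to show measurable changes". Section 2.6 cites a study in which the "relative abundance of Bifidobacterium species increased following the consumption of human milk oligosaccharides". Section 2.9 makes the relative abundance of blood YDB DNA over five time points the primary outcome.

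**Related rules.** Section 2.1 permits other dairy products during reintroduction. Section 2.7.2 uses faecal YDB, with questioning and a questionnaire, to judge withdrawal; participants who appear not to have withdrawn are excluded and replaced.

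**The concern.** The design draws its strength from introducing known organisms and watching for them. That works only if the measurement can tell the introduced organisms from others that look the same to it. A species label cannot distinguish LGG, LA-5 or BB-12 from another member of the same species, whether that member comes from a different dairy product or was already in the participant.

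Two readings of the results are exposed. A rise after reintroduction could be credited to the supplied cultures when it has another source. And a species that stays detectable at D0 (after the 10 dairy-free days) could be taken as a sign of hidden dairy intake, which in a trial of 10 could cost a compliant participant.

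**Working it through.** The protocol states no figure for resolution or background, so there is none to reproduce. The main check sets the sections side by side.

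1. **Target against read-out.** The Abstract, section 2.1 and the Discussion name cultures or strains. Section 2.8.2 ends at species. No strain-marker or strain-genome step appears, and clustering redundant genes beforehand can merge near-identical genes from related strains. As described, the pipeline can support a statement about species but not one about LGG, LA-5 or BB-12.

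2. **Sources of a species-level rise.** Three sources are compatible with the text: the study yogurt, other dairy (allowed in 2.1), and same-species organisms already present whose amount changes with diet. *L. lactis* shows the second. It is treated as dairy-dependent in general and is not among the three cultures named for the yogurt, so its return is evidence of dairy intake but not of the study yogurt in particular.

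3. **The genus wording.** Section 2.5.3 calls *Bifidobacterium* species dairy-dependent, while the study cited in 2.6 has them rising after oligosaccharides, an intake that is not described as supplying bacteria. On the protocol's own citation, the genus is not a specific marker of yogurt.

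4. **What the D0 sample removes.** Let R be same-species background DNA at D0 and Y the added yogurt DNA, with all other microbial DNA unchanged. If R is constant, the absolute change is still Y, and the apparent fold change is (R + Y)/R = 1 + 1/r, where r = R/Y. The values of r below are assumptions:

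| r | 0.1 | 0.5 | 1 | 5 | 10 |
|---|---|---|---|---|---|
| Fold change | 11 | 3 | 2 | 1.2 | 1.1 |

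A constant background dilutes the relative change and does not produce a rise. Only a background that moves with time or diet can do that.

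5. **If the background varies.** This is an illustration with a two-sided paired t-test at 0.05 and n = 10, not the planned repeated measures ANOVA. A power of 80% needs a standardised within-person change of d = 1.00 (0.996 before rounding). Let the background add independent within-person variation with an SD of k times that of the yogurt signal, so that d becomes 0.996/√(1 + k²). The values of k are assumptions:

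| k | 0 | 0.5 | 1 | 2 | 3 |
|---|---|---|---|---|---|
| d | 1.00 | 0.89 | 0.70 | 0.45 | 0.31 |
| Power | 80% | 71% | 51% | 24% | 14% |

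6. **Controls.** The spike-in shows whether yogurt DNA can be detected in blood. The placenta, virus, organoid, pig and rat controls address background and misclassification. None is described as separating a yogurt strain from another member of its species. The material for doing so is already planned, because the spiked samples, "together with non-spiked baseline blood DNA sample and pooled yogurt DNA, will undergo shotgun sequencing and taxonomic profiling".

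**The case against.** The strongest reply is that the inferential argument in 2.5.1 and 2.8.1 is made for species, which the pipeline does deliver. Under lowest-common-ancestor assignment, sequence shared between species moves up to genus and leaves the species count, so other *Bifidobacterium* species are largely kept out. Each participant has a D0 reference. Compliance does not rest on faecal YDB alone. The article is condensed, and section 2.8.1 allows a modified version of a published pipeline that is not shown. A species that rises in both stool and blood would still bear on whether blood follows the gut, whichever strain caused it.

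Most of this stands and limits the point. It does not remove the attribution to named cultures, and the modification mentioned in 2.8.1 is not said to include a strain step.

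A reader might infer more: that resident gut bacteria are scored as yogurt signal, or that the whole *Bifidobacterium* genus enters the primary outcome. The documents do not support this. The sentence in 2.5.3 is an expectation under the long-term objective, no section sums a genus into YDB, and 2.5.1 restricts YDB to organisms present only after dairy. Whether the three cultures' species have resident human members is not stated; where they have none, species-level assignment is enough to exclude residents. Nor do the documents say that the rise cited in 2.6 came from feeding residents, or that the study yogurt contains those oligosaccharides.

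**Conclusion.** The point holds as a mismatch between claim and resolution. The protocol names cultures as the signal and describes a species-level read-out. With other dairy allowed, a species-level rise cannot be assigned to the supplied cultures, and a persistent background at D0 can be mistaken for non-compliance. It does not show that the primary outcome is invalid or that a false rise is to be expected.

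The size cannot be derived from the documents. The fold changes of 11 down to 1.1 and the powers of 71% down to 14% show direction only and depend on assumed ratios. It is tempting to size the problem by BB-12's share of all *Bifidobacterium* in stool. With an assumed resident level of 1–10% and an assumed BB-12 level of 0.05–0.5%, that share runs from 0.05/10.05 = 0.5% to 0.5/1.5 = 33%. This should not be used as evidence: it is a genus-level stool figure, whereas the pipeline works at species level and the primary outcome is in blood.

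**What to change.** In sections 2.8.2–2.8.3:

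- List the YDB taxa at species level, not genus.
- Add a prespecified count, in blood and stool at every visit, of reads that match the study-yogurt genomes uniquely against near relatives in the reference database. Take the genomes from the pooled yogurt DNA already to be sequenced for Fig. 3A.
- Report this count beside the species-level count. Base any attribution to LGG, LA-5 or BB-12 on it; otherwise limit the claim to species.
- Use each participant's D0 count as the within-person reference. Do not mask genome regions seen in that participant's D0 stool: this would give each person a different countable genome, and it could delete the target if traces of yogurt DNA remain.

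In section 2.5.3, narrow *Bifidobacterium* species to the supplied organism.

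The cost is extra bioinformatics on data already planned, with no new samples or visits. The downside is sensitivity. Section 2.8.1 stresses the low microbial biomass of blood, and few reads there may be strain-unique, which is why the species-level count should stay. The added count also depends on recovering usable genomes from the pooled yogurt DNA, and it cannot separate the study yogurt from another product made with the same culture.

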#### Microbiome taxonomic analysis

2.8.3

Krona tool [39] will be used to visualize taxonomic abundance and generate clustered heatmaps. Principal component analysis (PCA) and non-metric multidimensional scaling (NMDS), using the R *vegan* package, will assess variation in microbiome composition. Analysis of similarities (ANOSIM) will test for significant differences between time points. Group-wise taxonomic differences will be identified using LEfSe, with permutation tests and multiple testing correction via the Benjamini–Hochberg false discovery rate. A p-value <0.05 will be considered statistically significant. YDB will be analyzed separately from the pooled shotgun metagenomic dataset due to its specific study relevance.

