#### Secondary objective(s)

2.5.2

To explore changes in the broader microbiome DNA landscape, including bacterial, viral, and archaeal DNA, in both fecal and blood samples before and after dairy consumption. This analysis aims to identify additional microbial signatures that may respond to dietary intervention and assess whether non-YDB microbial DNA in the blood mirrors corresponding shifts in the intestinal microbiome and yogurt consumption-induced effects on immune function.

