### Statistical analysis

2.9

The primary outcome is the change in relative abundance of blood YDB DNA across five time points. This will be analyzed using repeated measures ANOVA to detect statistically significant within-subject changes over time. The secondary outcomes include changes in all other non-human microbial DNA, which will also be analyzed using repeated measures ANOVA. All statistical tests will be two-tailed, with significance set at p < 0.05.

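### ANOSIM between time points (2.8.3) cannot tell a shift in composition from a difference in spread, so a significant result is not by itself evidence of a dietary shift

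*Protocol article*

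**What the plan says.** Section 2.8.3 of the protocol article plans PCA and NMDS in the R package vegan, which "will assess variation in microbiome composition". It then gives one community-level test: "Analysis of similarities (ANOSIM) will test for significant differences between time points". The threshold follows: "A p-value <0.05 will be considered statistically significant". LEfSe is named for individual taxa. The section names no test of dispersion and does not say how ANOSIM labels are permuted.

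The samples come from the same people at five visits. On the first, section 2.1 says: "At baseline, prior to any dietary intervention, blood and stool samples will be collected". The second follows ten days without dairy, and the last three fall in the yogurt phase, when other dairy is also allowed. The secondary objective (2.5.2) includes to "assess whether non-YDB microbial DNA in the blood mirrors corresponding shifts in the intestinal microbiome". Section 2.9 assigns the primary and secondary outcomes to repeated measures ANOVA, so ANOSIM is a supporting analysis.

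**The concern.** The scientific question is one of location: does the typical community change when dairy is withdrawn and yogurt is introduced, and does blood follow stool? ANOSIM permutes visit labels and compares ranked distances between visits with those within visits. Its null hypothesis is that visits have the same distribution, spread included. A visit that is merely more scattered can therefore give a small p-value.

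Unequal scatter is conceivable here. The first visit is on each person's own diet, and low-biomass blood may vary between visits for technical reasons. A significant ANOSIM in blood and in stool could then be read as matching dietary shifts when only the scatter differed.

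The pairing pulls the other way. If labels are permuted freely over all samples, similarity within a person makes the test conservative, and real shifts can be missed.

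**Working it through.** **Inputs from the document.** Ten volunteers (2.6: "we have chosen to include 10 volunteers for this study"), five time points (2.9: "The primary outcome is the change in relative abundance of blood YDB DNA across five time points"), alpha 0.05. The plan states no figure for ANOSIM, so there is none to reproduce.

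**Assumed, because not given.** Ratio of the T-10 SD to the SD at other visits: 1.5 to 2. Within-person correlation (ICC): 0, 0.2 and 0.5. Permutation free or within person. Euclidean or Bray-Curtis distance.

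**Step 1: why spread alone moves ANOSIM.** There are 10 × 5 = 50 samples and 50 × 49 / 2 = 1,225 pairs. Of these, 5 × 45 = 225 lie within a visit and 1,000 between visits. The statistic is R = (mean between-visit rank − mean within-visit rank) / (1,225 / 2). Take equal means, no subject effect, and SD 1.5 at T-10 against 1 elsewhere in every feature:

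| Pair | Within visit | Between visits | Expected squared distance per feature |
|---|---|---|---|
| Neither sample at T-10 | 180 | 600 | 1 + 1 = 2 |
| One sample at T-10 | 0 | 400 | 2.25 + 1 = 3.25 |
| Both samples at T-10 | 45 | 0 | 2.25 + 2.25 = 4.5 |

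With many features the three classes separate, and their mean ranks are 390.5, 980.5 and 1,203.
- Between visits: (600 × 390.5 + 400 × 980.5) / 1,000 = 626.5.
- Within visits: (180 × 390.5 + 45 × 1,203) / 225 = 553.
- R = (626.5 − 553) / 612.5 = 0.12, although no mean has moved.

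On squared distances, the scale PERMANOVA uses, the two averages agree: (600 × 2 + 400 × 3.25) / 1,000 = 2.5 and (180 × 2 + 45 × 4.5) / 225 = 2.5. This balance is particular to Euclidean distance and is not guaranteed for Bray-Curtis.

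**Step 2: what pairing does.** There are 10 × 10 = 100 same-person pairs, all between visits. If people resemble themselves, these pairs lower the between-visit mean. Free permutation would place on average 100 × 225 / 1,225 = 18.4 of them within a visit, so the observed R looks too low. Within-person permutation keeps all 100 between visits, which restores the 5% level under equal spread and leaves the effect in step 1 exposed.

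**Step 3: simulated rejection rates with no shift.** T-10 SD inflated in all 30 features, Euclidean distance. Ranges are over repeated runs.

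| SD ratio | Permutation for ANOSIM | ICC 0 | ICC 0.2 | ICC 0.5 |
|---|---|---|---|---|
| 1.5 | within person | 96–100% | 91–92% | 67–71% |
| 1.5 | free | 96–99.5% | 50–55% | 0% |
| 2 | within person | 100% | 100% | 100% |
| 2 | free | 100% | 100% | 56% |

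At ratio 1 the within-person tests reject 4% to 6%. Within-person PERMANOVA stays at 4% to 10% throughout this table.

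**Step 4: Bray-Curtis, within-person permutation, ratio 1.5 and then 2.** At ICC 0.5 ANOSIM rejects about 24% and 78%, against about 12% and 36% for PERMANOVA. Other data models with 50 taxa:
- Log-normal, subject SD equal to residual SD (ICC 1 / (1 + 1) = 0.5): ANOSIM 22% and 76%, PERMANOVA 14% and 47%.
- Dirichlet, moderate subject effect: ANOSIM 41% and 99%, PERMANOVA 12% and 37%.

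The level depends on the model and the number of taxa. The order of the two tests does not change in these settings.

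**Step 5: spread inflated in a few taxa only (Euclidean, within person).**
- 3 of 30 features: 5% to 7% at ratio 1.5 and 12% to 13% at ratio 2.
- 6 of 30 features: 6% to 12% at ratio 1.5 and 20% to 42% at ratio 2.

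**Step 6: power for a real shift (equal spread, ICC 0.5, Euclidean).** At 0.3 SD, free ANOSIM has 0% power, within-person ANOSIM 90% and within-person PERMANOVA 95%. In another simulation with shifts of 0.3 to 0.5 SD, free ANOSIM again had 0%, within-person ANOSIM 48% to 99% and within-person PERMANOVA 52% to 99.7%.

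**The case against.** Several objections carry weight.

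- **The design does not establish unequal spread.** A reader might infer that T-10 must be the most variable visit. The document does not say so. Only dairy is controlled, other dairy is allowed during the yogurt phase, and section 2.5.3 expects organisms that do not depend on dairy to stay fairly stable. The highest rates above need inflated spread in every taxon. This objection stands and limits the size of the point.
- **A false positive is not the usual outcome in every form of the test.** A reader might infer that a more variable visit will be declared a shift. With free permutation and ICC 0.5, the rate at ratio 1.5 is 0%. It is not a safeguard: at ratio 2 it reached 56% with 30 features and 92% with 50. The same conservatism also removes the power.
- **PERMANOVA is no cure.** With Bray-Curtis it still rejects too often when spread differs. This stands, and calling a shift on PERMANOVA alone would be unsafe.
- **The consequence is limited.** Section 2.8.3 speaks of differences, not of location, and nothing in the document rests the blood-to-stool comparison on ANOSIM; the Discussion refers to correlation analyses.
- **A fuller plan may give the permutation scheme and a dispersion check.** Their absence from a condensed article is not held against it. The point concerns the test that the article does name.

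**Conclusion.** The concern holds in limited form. ANOSIM cannot separate a compositional shift from a difference in spread, and equal group sizes do not protect it. If spread differs across most taxa (SD ratio 1.5 to 2, ICC 0.5, within-person permutation), false-positive rates are about 67% to 100% with Euclidean distance and 24% to 78% with Bray-Curtis. If only a few dairy taxa are affected, the inflation is small to moderate. If labels are permuted freely and people resemble themselves, the larger risk is a missed shift. The ratios, the ICC, the distance and the permutation scheme are all assumptions.

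The document does not support reading this as a prediction of false findings in this trial, or as a threat to its primary result. It is a weakness of a supporting analysis, worth correcting because the remedy is cheap.

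**What to change.** In 2.8.3, replace ANOSIM by PERMANOVA (adonis2 in vegan) with permutations restricted within participant. Beside it, report a dispersion test that respects the pairing (betadisper, permuted within participant).

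State the reading rule in advance. Call a result a compositional shift when PERMANOVA is significant and dispersion does not clearly differ. Where dispersion differs, report the result as a shift and/or a difference in spread, and support the reading with the ordination.

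The cost is a few lines of wording and other functions in a package already named. In the Euclidean settings simulated, power was not lost against within-person ANOSIM. Two limits remain: PERMANOVA with Bray-Curtis keeps some sensitivity to spread (about 12% at ratio 1.5 and 36% at ratio 2), and a dispersion test has low power with ten participants, so a non-significant result does not prove equal spread.

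### ANOSIM and LEfSe are planned across five repeated visits with no stated blocking by participant, and the false discovery rule given for LEfSe is not carried to the section 2.9 tests of the same non-YDB data

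*Protocol article*

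**What the plan says.** The design is within-subject: "We will perform a within-subjects crossover trial with a single arm". On size, "we have chosen to include 10 volunteers for this study", and sections 2.1 and 2.9 fix five sampling times.

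Section 2.8.3 (Microbiome taxonomic analysis) names the community-level and taxon-level tests: "Analysis of similarities (ANOSIM) will test for significant differences between time points. Group-wise taxonomic differences will be identified using LEfSe". The LEfSe sentence goes on to specify permutation tests and Benjamini-Hochberg correction. The next sentence sets the threshold: "A p-value <0.05 will be considered statistically significant". No pairing, blocking or restricted permutation is mentioned.

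Section 2.9 (Statistical analysis) takes up the non-YDB data again: "The secondary outcomes include changes in all other non-human microbial DNA, which will also be analyzed using repeated measures ANOVA". It closes with a general rule: "All statistical tests will be two-tailed, with significance set at p < 0.05". No multiplicity correction is named there. The document does not say which of the two sections carries the secondary conclusion.

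**The concern.** The five time points are the same people measured repeatedly. A comparison that treats visits as separate groups leaves stable differences between people in the error term, and those are what a within-subject design is meant to remove. The result is a test that rejects too rarely. A null ANOSIM result could then be read as evidence that blood does not respond to diet, when the test had little chance of showing a response.

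Section 2.9 has the opposite weakness. It uses a paired test, but if that test is applied taxon by taxon at an unadjusted 0.05 it will list taxa by chance. Section 2.8.1 itself treats false-positive microbial signals as the field's main difficulty, so an uncorrected list would be hard to defend. The same data thus have two analyses that differ in both pairing and multiplicity.

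**Working it through.** **Plan's own figure.** The 10 volunteers were chosen by analogy with two published studies of 6 and 7 volunteers. No effect size, SD, ICC or power is given, so there is no stated operating characteristic to reproduce.

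**Inputs from the document.** 10 participants × 5 visits = 50 samples per compartment (blood or feces); alpha 0.05, two-sided.

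**Assumptions.** ICC 0 to 0.8; normal data; Kruskal-Wallis stands in for the group-wise step of LEfSe; 20 to 1,000 taxa.

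**1. Single taxon, effect fixed in total SD.** A shift of 0.8 total SD is placed at D1, D2 and D7, with 40,000 runs per setting. In within-person units the shift is 0.8/√(1 − ICC), for example 0.8/√0.5 = 1.13 at ICC 0.5.

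| ICC | Shift in within-person SD | Kruskal-Wallis null size | Kruskal-Wallis power | Friedman power |
|---|---|---|---|---|
| 0 | 0.80 | 4.4% | 49% | 42% |
| 0.3 | 0.96 | 1.2% | 43% | 57% |
| 0.5 | 1.13 | 0.3% | 39% | 74% |
| 0.7 | 1.46 | 0.03% | 36% | 94% |
| 0.8 | 1.79 | 0.01% | 35% | 99% |

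Friedman null size stays between 4.2% and 4.6% throughout.

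**2. Same question, effect fixed in within-person SD.** Paired power in step 1 rises partly because the shift grows in within-person units. With a drop of 1.5 within-person SD at D0 only (20,000 runs), Kruskal-Wallis power at ICC 0, 0.3, 0.5, 0.7 and 0.8 is 87%, 69%, 46%, 16% and 5%. Friedman stays at 78 to 79% and repeated measures ANOVA at 90 to 91%. The loss from ignoring the participant does not depend on the scaling; its size does.

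**3. ANOSIM.** Bray-Curtis distances, 40 taxa of which 8 drop at D0 by 0.75 to 1.5 within-person SD on the log scale, ICC 0.5 and 0.8, 300 runs, 199 permutations. Free permutation rejects in 0 to 1% of runs in every setting. Permuting within participant gives 14% to 93% power: at the 1.5 SD drop, 93% at ICC 0.5 and 67% at 0.8. Its null rejection rate is 2% and 6% respectively.

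**4. Chance hits in section 2.9.** With no true change, expected hits = 0.05 × m for m taxa, and the chance of at least one is 1 − 0.95^m if tests are independent.
- m = 20: 1 hit, 64%
- m = 100: 5 hits, 99%
- m = 200: 10 hits, about 100%
- m = 1,000: 50 hits, about 100%

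Benjamini-Hochberg at 5% over 200 null taxa cuts the mean from 10.0 hits to about 0.06.

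**The case against.** A reader might infer that the plan treats the 50 samples as independent. The text does not say so: it is silent on the permutation scheme, and a within-participant restriction could sit in an analysis plan that is not shown. This stands, and the power loss is therefore conditional on the tests being run in their usual unpaired form.

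A reader might also infer that most power is lost. That needs an ICC the document does not give. Section 2.5.3 expects non-dairy organisms to be fairly stable, which suggests a high ICC; the low biomass and contamination described in section 2.8.1 suggest a lower one in blood. At ICC 0 the unpaired test is no worse.

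Nor is the within-subject design discarded. Section 2.9 gives the secondary outcomes a paired test, while ANOSIM and LEfSe sit beside heatmaps and ordination as supporting analyses. It would also be wrong to say that the plan has no false discovery control, since LEfSe has it. That the two sections would give conflicting answers for the same taxa is not shown; ANOSIM has no per-taxon output.

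The secondary analysis in section 2.9 could also mean an aggregate rather than one test per taxon. The per-taxon reading is likelier, because section 2.8.2 promises abundances for every taxon.

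What the objection leaves standing is that a group-wise LEfSe comparison is named for paired data, and that the correction in 2.8.3 is absent from the section that sets the threshold for the secondary outcomes.

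**Conclusion.** The point holds in limited form. If unpaired, the section 2.8.3 tests are over-conservative to a degree set by an unknown ICC. The single-taxon loss is nil at ICC 0, moderate at 0.3, and close to half of the paired power at 0.5 (39% against 74%) under the total-SD scaling, and greater above that. Free-permutation ANOSIM had almost no power in the settings run, all at ICC 0.5 or 0.8. Error in this direction hides change; it does not create false findings.

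If section 2.9 is applied per taxon, about 5 false hits per 100 taxa are expected when nothing changes; the taxon count is an assumption.

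The primary outcome, blood YDB by repeated measures ANOVA, is not affected, and these are secondary analyses in a pilot. The change is still worth making because it is cheap and can be settled before any data are seen.

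**What to change.** 1. State that ANOSIM permutations are restricted within participant. PERMANOVA with the same restriction is an option, but it is not needed to cure the defect.
2. Replace the unpaired LEfSe comparison by a paired taxon test, or by a model with a participant random effect.
3. Extend the Benjamini-Hochberg rule to the secondary analyses of section 2.9: q < 0.05 across all tested taxa within each compartment.
4. State that the section 2.9 analysis carries the secondary conclusion and that the section 2.8.3 tests support it.

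The cost is a few sentences and different software calls, with no new samples, visits or participants. The downside is fewer nominally significant taxa in the section 2.9 list.
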